#### The creams

2.2.5

The intervention creams are Oviderm (Oviderm 25 % cream, Galenica AB, Sweden) and Canoderm (Canoderm 5 % cream, ACO HUD Nordic AB, Sweden), are used as moisturizing treatment for dry skin. Oviderm contains propylene glycol at a concentration of 25 %, while Canoderm contains 5 % propylene glycol and 5 % urea. Both propylene glycol and urea are low molecular weight substances with water attracting properties and therefore normally described as humectants with good capacity to improve skin hydration [17]. In addition, urea is keratolytic and used at high concentrations for the treatment of hyperkeratotic skin disorders [17]. Propylene glycol on the other hand, is widely used in pharmaceutical formulations as a solvent, or vehicle, for substances with low solubility in water and also demonstrated to have penetration enhancing properties [18]. Propylene glycol in this concentration (25%) has additionally some antimicrobial properties [19]. Studies have also shown that urea and propylene glycol enhances the molecular mobility skin barrier lipids and keratin filaments at relatively dry conditions [20,21]. Notably, this effect is not solely due to increased water content of the skin but rather appears to be related to preserved fluidity of the skin barrier molecular components under dehydrating conditions [20]. Urea is also known for its skin barrier strengthening effect [22]. The comparator, Decubal lipid cream (Decubal Lipid Cream, Karo Healthcare AB, Sweden), does not contain humectants. Nonetheless, it effectively forms a semi-occlusive barrier on the skin, minimizing water loss through vaporization and thereby enhancing hydration. This effect should be common to all three creams employed.

#### Package, labelling and storage

2.2.6

##### Package

2.2.6.1

All three creams will be filled into similar pump containers to ensure the blinding process. The filled containers will be packed as kits. Each kit will contain two containers, with two different creams, either Oviderm together with Decubal lipid cream or Canoderm together with Decubal lipid cream. One of the kit type will be given to each participant after the randomization procedure.

##### Labelling

2.2.6.2

The filled cream containers will be labelled as well as the card box kit package. This will be done in accordance with the Swedish Medicines Agency collection LVFS 2011:19 (https://lagen.nu/lvfs/2011:19), §7, page 15. The container in the kit will be marked with the foot to be treated (right or left).

##### Storage

2.2.6.3

The study creams will be stored at the Contract Research Organisation (CRO), Bioglan AB Malmo, Sweden and the research team will order the products when needed. The study creams should be kept in a room with maximum temperature of 25 °C. The study participants will be informed about this.

### Intervention

2.3

If the participants are using any topical products (i.e. oils, ointments, creams or gels) a wash-out period of two weeks is needed. All participants will be assessed against inclusion-exclusion criteria and if eligible they will be asked in the welcome letter to discontinue treatment for two weeks and to return to the study clinic. The welcome letter will inform them about the address and time and date for the appointments. If they have not used any foot cream for the last two weeks and are judged eligible, they will be assessed for a number of parameters including skin barrier characteristics, criteria, and randomized already at the first visit. The participants will receive a kit with two identical containers, marked “left foot” and “right foot”. The participants will be informed about the importance to use the same marked container for the same treatment area during the whole study period. After application on one foot, the participants need to wash their hands, which they also will be informed about. The study creams (described below) will be applied on the feet twice a day. Each participant will be asked to mark the calendar each morning and evening when having applied cream in an individual schedule, which will be distributed at the start of the study.

The efficacy (the difference of change in xerosis between baseline until 4 weeks post baseline between intervention and comparator groups), and safety, between Oviderm cream against Decubal lipid cream in one arm, and Canoderm cream against Decubal lipid cream in the other arm, will be evaluated. The study trial period of four weeks was chosen based on shown effects in the intervention arm in previous RCTs [13,14] on foot xerosis in persons with diabetes mellitus.

#### Outcomes

2.3.1

##### Primary outcomes

2.3.1.1

The primary outcome in this study, which the power calculations are based on, is the change in xerosis (dry skin), after four-week application of creams containing humectant compared to humectant-free cream on the diabetic feet. XSS score will be assessed and evaluated at baseline, i.e., visit 1 or 2 (if washout period needed), visit 2/3 (after two weeks after baseline-week application) and visit 3/4 (four weeks after baseline). Assessment will be performed using the 7-graded (from 0 to 6) XSS score. The classification of the scale is described in Table 1. Foot xerosis severity will be determined based on the most severe located dryness of the foot, and this location will be documented in REDCap.

**Table 1 tbl1:** The xerosis severity scale.

Classification	Description	Category
Mild	Normal Skin	0
	Dusty appearance, occasional minute skin flakes	1
	Generalized dusty appearance, many minutes skin flakes	2
Moderate	Defined scaling with flat borders	3
	Well defined heavy scaling with raised borders, shallow fissures	4
Severe	Large scale plates, fissures	5
	Large scale plates, deep erythematous fissures	6

Digital photographs with Canon EOS (Electro-Optical System) 750D, Canon Inc, Tokyo, Japan of the participants' feet will be taken for documentation in REDCap to be objectively evaluated by a dermatologist, and for XSS validation, by a second dermatologist. The Canon EOS 750D is capable of producing great photos and has been updated with a 24.2 megapixel sensor and built in Wi-Fi making it an excellent entry level DSLR (digital single-lens reflex camera). In a report published in 2018, a DSLR camera was successfully used to visually classify heel xerosis grade using similar xerosis assessment scale as outlined in the present study protocol, and to evaluate the effects of moisturizer on heel skin dryness [23]. The dermatologists will not have any personal contact with the study participants and will be blinded to cream exposure to evaluate dryness of the feet.

##### Secondary outcomes

2.3.1.2

The secondary outcomes are supporting evidence of differences in efficacy of creams on skin barrier integrity, and changes in health-related quality of life during the study period. Skin barrier integrity and hydration will be obtained by non-invasive biophysical measurements as follows.•Trans epidermal water loss (TEWL) is a key indicator of the barrier function of the stratum corneum (SC). Elevated TEWL typically indicates a compromised skin barrier, while lower TEWL is associated with good SC barrier properties and healthy skin [24].•Skin hydration by measurement of skin impedance (skin resistance and skin capacitance). It is well-known that maintaining healthy skin relies heavily on adequate skin hydration [25]. Standard methods for assessing skin hydration involve measuring the skin's electrical properties, which vary with the skin's water content. In this work, the skin hydration will be assessed by measuring the resistance and capacitance by electrical impedance spectroscopy [26]. Increased skin capacitance (increased dielectric constant of skin) indicates higher skin hydration; thus healthier skin barrier [26].•Skin surface pH provides an indication of host-microbiota interaction. Acidic pH value (*e.g.*, pH 5.5) is usually related to the dominance of commensal bacteria on the skin. Shifting skin surface pH towards basic values (*e.g.*, pH 6.8) might indicate an increased inhabitance of skin by pathogenic microbiota [27].•Health related quality of life assessed with EuroQoL 5 level (EQ-5D-5L) instrument.

To support the outcomes by molecular characteristics of skin and physiological health parameters relevant to diabetes the following assessments will be made.•Macrocirculation measured as ankle-brachial index and toe-brachial index. Microcirculation including transcutaneous oxygen pressure (Laser doppler/transcutaneous O_2_ -electrode/laser doppler flow with heat provocation) (Peripheral circulation is measured by Periflux 6000 combined; Perimed AB, Stockholm, Sweden)•Degree of neuropathy (multi-frequency vibrametry) (VibroSense Meter; VSM II, Vibrosense Dynamics AB, Malmö, Sweden). Assessment of vibration perception threshold at 125 Hz with multi-frequency vibrometry has shown to have a strong correlation with nerve conduction studies in diabetic peripheral neuropathy [28].•Molecular biomarkers including microbiota will be analyzed after a non-invasive sampling from the surface of the skin.•HbA1c by using a stick test for collecting capillary blood in the middle finger.•XSS scores are determined by study investigators at study inclusion and will be validated by a dermatologist. Photographs of the feet will be taken to validate XSS grading and for documentation of the colour and surface structure of the skin.

### Data management

2.4

For the current study data will be entered into and monitored in REDCap, version 13.1.37. The study is divided into four phases: *Screening, Initial evaluation and randomization, Treatment and Final evaluation.* The collection of data will run over a period of four weeks. Data that will be collected during the screening, visit 1 at the study clinic, will be year of birth, gender, specification of diabetes type, year of diabetes diagnosis, medical history, medication, date of study entry and concomitant medication. Health declaration will be collected and informed consent will be signed. All participants will be asked on forehand (Welcome letter and in the phone call) to have a washout period of 14 days before the first visit at the study clinic. If the participants have not used creams (have had their wash-out period) for two-weeks, visit one and visit two will be merged and baseline data will be collected (see below for descriptions). If the participants need to come back after the washout, that will be the second visit for them. Baseline data will include; XSS with photos, TEWL, hydration, skin pH, Vital signs, circulation tests (both micro and macro), neuropathy, collection of low molecular biomarker and microbiota from the surface of the skin, HbA1c, Health-related Quality of Life (EQ-5D, the Swedish tested version, with approved registration number 46933), adverse events, product accountability. Seven days after the baseline the participants will be contacted over phone by the research nurses. Approximately 14 days (12–16 days) after baseline data is collected, XSS with photos, TEWL, hydration and skin pH will be taken.

At the last visit 26–30 days after the study start, the same tests will be conducted as during visit 1 (Table 2).

**Table 2 tbl2:** Flowchart of the studyplan and collection of the data.

Events	Visit 1 Screening & Baseline (if washout period is not needed) 120 min	Visit 2 Baseline (if wash-out period is needed) Day 0 100 min	Phone call Day 7 (5–9) 30 min	Visit 3 Day 14 (12–16) 60 min	Visit 4 Day 28 26–30 120 min
Signing Consent form	x				
Allocation of study number	x				
Eligibility criteria	x				
Demographic data	x				
Medical history of diabetes	x				
Comorbidity (Health declaration)	x				
Concomitant medication	x				
Extra eligibility test if 2-weeks wash-out	x	x			
Neuropathy	x	x			x
Macro-and Micro circulation	x	x			x
Vital signs	x	x			
Dispensing of study product kit	x				
Weight of cream container	x	x		x	x
XSS including photography of the foot	x	x		x	x
TEWL	x	x		x	x
Skin hydration/Impedance	x	x		x	x
Skin pH	x	x		x	x
Molecular biomarkers sampling from skin	x	x			x
Microbiota sampling from skin	x	x			x
Analysis of HbA1c by prick test	x	x			x
Adverse Events	x	x	x	x	x
EQ-5D-5L	x	x			x
Product accountability	x	x	x	x	x

Visits at the study clinic will be scheduled by the study investigators together with the study participants, according to a time schedule. The participants will be asked about any adverse events during all visits and over the phone call.

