#### Enrollment and randomization

2.2.3

Persons with diabetes will be introduced about the study at society meetings and at social media. Potential study participants that are suitable (according to the study criteria) for the study will be contacted and informed in more details about the study by the research nurses. Furthermore, a welcome letter will be sent by post to the participants with practical information. If acceptance and pass of criteria, informed consent form will be signed and the potential participants will be recorded in the research software program Research Electronic Data Capture® (REDCap) version 13.1.37. The participants will then be randomized and will adhere to the clinical study schedule and specific study procedures. The enrolled study participants will be given an autonomic code (in REDCap) as soon as the participants have signed the consent form. According to the code the participants will be randomized into different treatment, unknown which, for both the participants and the investigators (double-blind). Apart from the treatment randomization the participants will be randomized to which foot that will be treated with which cream. One foot will be treated with one interventional cream (cream A or B) and the contralateral foot with the comparator humectant-free cream (C).

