### Ethical consideration

2.7

Signed informed consent forms will be obtained from all participants prior to the study start. The study has been approved by the Swedish Medical Products Agency, application number 2022-500907-27-01-SM (substantial modification −1), date of approval 20231101. This RCT is registered the 23 of April 2024, at ClinicalTrials.gov (https://clinicaltrials.gov): Identifier: NCT06427889.

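### Foot-cream users are asked to complete a 14-day wash-out before the first clinic visit, but signed consent is placed only at that visit

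*Protocol article*

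**What the plan says.** Section 2.4 (Data management) says that all participants will be asked beforehand, in the welcome letter and by phone, "to have a washout period of 14 days before the first visit at the study clinic". For the screening visit, which is Visit 1 at the clinic, the same section states: "Health declaration will be collected and informed consent will be signed". Table 2 marks the row "Signing Consent form" at Visit 1 and nowhere else.

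Section 2.4 also keeps a second route: "If the participants need to come back after the washout, that will be the second visit for them". Someone who arrives without a wash-out signs at Visit 1, washes out, and has baseline at Visit 2.

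Three other places bear on the order:

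- Section 2.2.3 (Enrollment and randomization) has research nurses inform suitable people, then says that "a welcome letter will be sent by post to the participants with practical information". It describes consent after that, once the criteria are passed. Entry in REDCap and the participant code go with the signature.
- Section 2.3 (Intervention) says that people are assessed against the criteria and that "if eligible they will be asked in the welcome letter to discontinue treatment for two weeks and to return to the study clinic".
- Section 2.7 (Ethical consideration) says: "Signed informed consent forms will be obtained from all participants prior to the study start".

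**The concern.** Stopping foot cream is a study requirement here and not part of usual care. Section 2.2.2 excludes anyone who has used topical moisturizers on the feet in the previous two weeks. The Introduction describes emollient use as advice that health professionals give to people with diabetes, and it links dry, cracked skin to ulcer risk. A request to suspend that care for two weeks is a study procedure, and one would expect signed consent before it.

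Two things are at stake. The first is that a participant changes recommended care for the study before agreeing in writing to take part. The second is traceability: a person who washes out, has a foot problem or loses interest, and never comes to Visit 1 has signed nothing and has no REDCap entry. This is a matter of participant protection and of clear instructions to staff. It does not bear on the treatment comparison.

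**Working it through.** No figure in the plan is in dispute, so the check is of sequence.

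**Step 1. Order of events on each route for a cream user.**

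| Event | Wash-out before Visit 1 (the section 2.4 request) | Wash-out between Visits 1 and 2 (section 2.4 fallback, Table 2) |
|---|---|---|
| Request to stop cream | letter and phone call, before any visit | same request, not yet acted on at Visit 1 |
| Signed consent | Visit 1, after the wash-out | Visit 1, before the wash-out |
| Days off cream at the study's request before consent | 14 | 0 |
| Adverse-event enquiry at the end of the wash-out | yes, merged Visit 1 | yes, Visit 2 |
| Clinic visits | 3 (Days 0, 14, 28) | 4 |

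The first column is what section 2.4 asks of everyone. The second applies to those who did not do it. The more closely a cream user follows the request, the later consent falls relative to the wash-out.

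**Step 2. Does another section move consent earlier?** Section 2.2.3 has the letter before the signature and makes the signature follow the eligibility check. The abstract speaks of enrolment after the two-week wash-out where one is needed. Neither places consent before Visit 1.

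**Step 3. Does section 2.3 give a different order?** Its wording about going back to the clinic suggests an earlier attendance, which would put the wash-out after Visit 1. But it makes the request in the welcome letter, the same vehicle as section 2.4, and it does not say where or how the criteria are assessed. It can be read either way.

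**Step 4. Does section 2.7 settle it?** It promises consent before the study starts. Section 2.4 schedules the last visit at 26 to 30 "days after the study start, the same tests will be conducted as during visit 1", and Table 2 gives that window to the Day 28 visit, so in that sentence the start is Day 0. If section 2.7 uses the term in the same way, consent after the wash-out but before Day 0 treatment would satisfy it. If it means something earlier, section 2.4 and Table 2 do not deliver it. Either way the order in section 2.4 stands uncorrected.

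**Step 5. Who leaves no record?** Under section 2.2.3 the REDCap entry and code come with the signature. Under section 2.4 and Table 2 no adverse-event contact is scheduled before Visit 1. A person who stops cream and never attends therefore has no consent, no code and no enquiry. This is an inference from the stated rules; the article gives no frequency.

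**The case against.** The strongest case against is that this is a condensed article. The full protocol, which the article says the Swedish agency approved, may send out consent forms earlier, and nurses do inform candidates in detail before the wash-out. That would be decisive if the article were merely silent. It is not: it states when the wash-out happens and when the form is signed, and the stated order is the wrong way round. Prior information is to the plan's credit but is not signed consent.

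Four stronger readings are tempting, and the documents do not support them.

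- A reader might infer that sections 2.3 and 2.4 flatly contradict each other. They do not clearly do so. The difference rests mainly on one verb in section 2.3, and the three enrolment descriptions can be read as one order: pre-screening, letter with the request, clinic.
- A reader might infer that wash-out events go unrecorded on one route. For anyone who attends, both routes have an adverse-event enquiry, an eligibility check and foot photography at the visit that ends the wash-out. An enquiry before the wash-out could not detect events during it. The gap is confined to people who never attend.
- A reader might take 14 of the 14 + 28 = 42 days from stopping cream to the last visit, or 33%, as the size of the problem. That is a share of the calendar and measures no risk, bias or loss.
- A reader might infer that nobody looks at the feet before the wash-out. Section 2.3 leaves room for such a check, so its absence cannot be claimed.

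It is also fair to object that moving consent forward has a knock-on effect. Section 2.2.3 issues the code on signature and randomises according to the code, so earlier consent could bring allocation ahead of the clinic eligibility check. That stands, and the fix has to deal with it.

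**Conclusion.** The point holds as one of participant protection and wording. A cream user who follows section 2.4 completes a 14-day, study-required break in recommended foot care before signing consent, against 0 days on the Visit 1 then Visit 2 route. Those who drop out during that break and never attend leave no study record.

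The number affected cannot be derived. The article does not say how many participants use foot cream or how many will follow the request, so among the 98 planned it could be anything from none to all, plus any who wash out and are never enrolled. No size of harm is claimed. Sample size, endpoint, analysis and efficacy inference are unaffected.

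The conclusion assumes that section 2.4 and Table 2 describe actual practice. It would fall away if the full protocol, not shown here, takes signed consent before the letter and call.

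**What to change.** Reword the request in section 2.4 and align sections 2.2.3 and 2.3 with it, so that cream users are asked to stop for 14 days only after signed consent has been received. There are two ways to do this:

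1. Remote consent alongside the welcome letter and phone call already planned, with the request to stop given once the signed form is in. Visit 1 remains the merged screening and baseline visit.
2. Consent at Visit 1, then the wash-out, with the existing Visit 2 as baseline.

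In both cases, record adverse events from consent and open a screening record at that point. Keep code allocation and randomisation after the clinic eligibility check at baseline. This means changing the sentence in section 2.2.3 that issues the code on signature. Under the second option, Table 2 also needs attention, because it marks study-number allocation and kit dispensing at Visit 1 only. Possible text: Participants who use foot creams will be asked to stop for 14 days only after their signed consent has been received; adverse events are recorded from consent, and randomisation follows confirmation of eligibility at baseline.

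The first option costs an earlier consent step and slightly more adverse-event recording, and the changed step may need to be notified to the approving body. The second takes a cream user from 3 clinic visits to 4, at most 100 extra minutes by the Visit 2 length in Table 2. The Discussion already warns that three visits may be hard to keep, so the first option is the lighter one. Whether and for how long creams are stopped remains a clinical decision.

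### Table 2 dispenses the kit at Visit 1 only, which conflicts with section 2.3 for participants who need washout and have their Day 0 and repeat eligibility test at Visit 2

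*Protocol article*

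**What the plan says.** The protocol article describes two routes into the trial. Participants with no recent use of topical products have screening and baseline combined at Visit 1. The others come back after two weeks, and for them Table 2 heads the column "Visit 2 Baseline (if wash-out period is needed) Day 0 100 min".

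Table 2 (section 2.4) marks these events before treatment:

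- "Signing Consent form": Visit 1 only.
- "Extra eligibility test if 2-weeks wash-out": Visit 1 and Visit 2.
- XSS with photography, TEWL, impedance, pH, circulation, neuropathy and the other baseline measures: Visit 1 and Visit 2.
- "Dispensing of study product kit": Visit 1 only.

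Three sections bear on when randomisation happens:

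- Section 2.2.3 says that enrolled participants "will be given an autonomic code (in REDCap) as soon as the participants have signed the consent form", and then: "According to the code the participants will be randomized into different treatment, unknown which, for both the participants and the investigators (double-blind").
- Section 2.2.6.1 says that each participant receives one of the two kit types once randomised.
- Section 2.3 says of people who have used no foot cream for two weeks that, if "judged eligible, they will be assessed for a number of parameters including skin barrier characteristics, criteria, and randomized already at the first visit".

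Section 2.5 makes intention-to-treat the primary analysis principle.

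**The concern.** The visit schedule is the part of a protocol that site staff work from. Here it disagrees with the text on the order of three steps for one group of participants: the last eligibility test, randomisation and supply of the creams.

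The order matters for two reasons. First, eligibility depends on the XSS score of each foot (two to six) and on the feet differing by no more than one point (section 2.2.1). Both can change while topical products are stopped. If allocation comes first, a person who fails the repeat test is already a randomised participant. The trial must then either drop that person, against its stated principle, or analyse someone who did not meet the entry criteria. Second, the primary outcome is change in XSS from baseline. Under early supply, a participant would hold creams labelled by foot during the weeks meant to be free of topical products, before the baseline is measured.

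**Working it through.** The plan gives no figure on this point, so the check sets the sections side by side.

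**Step 1. Is the single mark likely to be a table-reading fault?** The rows just before the dispensing row in Table 2 (neuropathy, circulation, vital signs) and those just after it (container weight, XSS, TEWL) keep their columns and carry marks at both Visit 1 and Visit 2. The table's convention for something done at baseline on either route is a double mark. The dispensing row departs from it.

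**Step 2. What does the table imply for a washout participant?**

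| Step | Source | Visit |
|---|---|---|
| Consent | Table 2 | 1 |
| REDCap code | 2.2.3, on signing consent | 1 |
| Kit supplied | Table 2 | 1 |
| Randomisation | 2.2.6.1, before the kit | no later than 1, if the kit is supplied at 1 |
| Repeat eligibility test | Table 2 | 2 |
| Baseline (Day 0) | Table 2 | 2 |

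Followed literally, randomisation and supply come about two weeks before the repeat test and Day 0. If the Visit 1 mark is meant only for people whose visits are merged, washout participants have no dispensing visit in the table.

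**Step 3. What does the text imply for the same participant?** Section 2.3 makes randomisation at the first visit conditional on no recent cream use, and the word *already* implies that the others are randomised later. Section 2.4 places randomisation in a phase after screening. The abstract says that enrolment follows washout where washout is needed. Together these point to Visit 2.

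**Step 4. Does section 2.2.3 settle it?** No. It says when the code is issued and that allocation follows the code. It does not say at which visit a washout participant is allocated. It also has the criteria passed before consent, without saying whether that includes the test after washout.

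**Step 5. Does any other row settle it?** Container weight and product accountability are marked at both visits. That fits a kit handed over at Visit 2, and equally a kit handed over at Visit 1 and brought back.

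**Step 6. How could someone fail the repeat test on XSS?** The scale runs from 0 to 6 and the eligible range is 2 to 6, so the upper limit cannot be breached. Failure needs a foot below 2 or a between-foot difference above 1.

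**Step 7. How many would be affected?** This needs the share who require washout and the share of those who fail the repeat test. The document gives neither.

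**The case against.** The strongest reply is that the intent is clear and one mark is missing. Sections 2.3 and 2.4 and the abstract all point to randomisation at Visit 2 for washout participants. Since the kit follows randomisation, a Visit 2 kit follows too. This is the likeliest explanation, and it stands as a statement of intent. It does not remove the conflict, because the schedule says otherwise and no sentence states when these participants are randomised or supplied. Nor is this detail that a condensed article has merely left out: the article prints the schedule, and the schedule disagrees with its text.

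Four stronger readings are tempting and are not supported:

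- *Randomisation is fixed at consent.* A reader might infer this from section 2.2.3. The sentence gives the basis of allocation, not its timing, and Table 2 lists allocation of a study number at Visit 1, which may be all that the code is.
- *Early randomisation is planned.* Section 2.3 points the other way.
- *The trial will lose a calculable number of participants, and power with them.* Both rates would have to be invented. Section 2.4 asks everyone to wash out before the first visit, so Visit 2 may serve few. The sample size already allows for 20 % not fully evaluable (78/0.8 = 97.5, rounded up to 98), and that allowance might absorb such losses. Under intention-to-treat they might not be excluded at all.
- *The baseline XSS will be contaminated.* That needs early supply and also use of the cream against the instruction to stop topical products. It is a risk of the literal schedule, not an expected result.

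**Conclusion.** The point holds as an internal contradiction. Table 2 supplies the kit at Visit 1 only. Section 2.3 implies that washout participants are randomised, and so supplied, at Visit 2. Section 2.2.3 does not decide between them.

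The consequence is conditional. If the table is followed, anyone who fails the XSS criteria after washout has already been allocated, and the analysis must breach either intention-to-treat or the entry criteria. If section 2.3 is followed, the problem does not arise.

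The size cannot be estimated from the document and may be small. The conclusion rests on taking the single mark in the dispensing row as printed, and on section 2.2.6.1 placing the kit after randomisation. It does not depend on any assumed rate, and no effect on power is claimed. The point is modest but worth correcting, because it lies in the schedule that staff will use and touches the baseline of the primary outcome.

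**What to change.** Reconcile Table 2 with sections 2.2.3 and 2.3:

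- State once, in section 2.2.3, that randomisation and kit dispensing take place at each participant's Day 0 visit (the merged Visit 1, or Visit 2 after washout), and only after the last eligibility test has been passed.
- Say in the same place that the code issued at consent does not itself trigger allocation, if that is so.
- Correct the dispensing row of Table 2 so that it shows the Day 0 visit of both routes, and add a randomisation row marked in the same way.

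The cost is one corrected table row, one added row, a sentence or two of text, and a check that REDCap releases the allocation at the Day 0 visit. The sample size and the analysis do not change.
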